## Abstract

**Background:**

Following horrific or life-threatening events approximately 10 to 15% of young children develop post traumatic stress disorder (PTSD). The symptoms of this disorder are distressing - nightmares, flashbacks, anger outbursts and disturbed play. These symptoms cause major disruption to a child’s functioning and, if left untreated, can persist for many years. As yet, there are no established empirically-validated treatments for PTSD in young children. Trauma-focused cognitive behaviour therapy (TF-CBT) is a psychological intervention that is effective in treating the disorder in older children (8 to 12 years), adolescents and adults. This study examines TF-CBT adapted for children aged between 3 and 8 years.

**Methods/Design:**

This protocol describes a two-arm exploratory randomised controlled trial comparing TF-CBT to treatment as usual (TAU) in children aged 3 to 8 years with a principal diagnosis of PTSD following a single-event discrete trauma. Using a half-crossover design, 44 participants will be randomly allocated to receive the intervention or to receive TAU. Those allocated to TAU will be offered TF-CBT at the end of the ‘treatment’ period (approximately 12 weeks) if still indicated. The primary outcome is PTSD diagnosis according to DSM-5 criteria for children 6 years and younger at post-treatment. Secondary outcomes include effects on co-morbid diagnoses and changes in emotion and trauma symptoms at each of the follow-up points (post-treatment, 3-months, 12-months). Additionally, broader efficacy will be considered with regard to treatment feasibility, acceptability and service utilisation. The key targets of the intervention are trauma memory, the interpretation of the meaning of the event, and the management of symptoms.

**Discussion:**

This is the first European trial to examine the efficacy of TF-CBT in alleviating PTSD in very young children. As well as providing much-needed data on the utility of the intervention, this exploratory trial will also allow us to gather important information about the feasibility of delivering the treatment in UK National Health Service (NHS) settings, and its acceptability to the children and their families. This study will highlight aspects of the intervention that need improvement or modification in preparation for a full-scale evaluation in a larger sample.

**Trial registration:**

ISRCTN35018680, registered on 18 November 2013.

## Background

Post traumatic stress disorder (PTSD) is a deeply distressing and disabling anxiety disorder comprising symptoms of trauma re-experiencing (for example, flashbacks, nightmares), avoidance (for example, social withdrawal, emotional numbing), and hyper-arousal (for example, anger outbursts). Children, like adults, can develop PTSD following exposure to a number of discrete traumatic events, including interpersonal violence, road traffic collisions and burns [1-3]. Until the publication of the Diagnostic and statistical manual of mental disorders 5th edition (DSM-5: [4]) the diagnostic criteria had been adult-orientated, which led to an under-diagnosis of PTSD when compared to more developmentally sensitive criteria [5]. Young children have a limited ability to convey their subjective experiences, as a result of their limited cognitive and expressive language skills [6] and consequently it has been necessary to focus on more behavioural markers of distress. Young children typically display a different range of behaviours to adults, which Carpenter and Stacks summarised as including: refusal to eat or trouble keeping food down; extreme difficulty falling asleep or frequent night-waking; or changes in responsiveness to an adults efforts to soothe them that may include responding with heightened irritability, fearful expressions, crying or blank expressions under circumstances that do not normally produce these effects (that is face-to-face play or efforts to comfort) [7].

PTSD is frequently co-morbid with other psychiatric conditions such as anxiety and depression and markedly impairs educational, social and daily functioning [5]. Traumatic events are experienced by up to two thirds of children by age 16 [8] including in preschool and early school years, even when excluding abuse. A significant proportion (10 to 40%) of these younger children who are exposed to non-abuse traumas are severely affected and go on to develop PTSD [3,9-12]. For example, 10 to 14% of 3 to 8 year-old children are diagnosed with PTSD when assessed with developmentally appropriate criteria 6 months after presenting at a UK Emergency Department (ED) following acute trauma [3]. There is evidence that if left untreated, PTSD in children and young people can lead a chronic course lasting a number of years [13]. In support of this, 10 to 15% of 3 to 8 year-olds have previously been found to have PTSD 3 years after a trauma, which is in line with consensus in the field that chronic PTSD in young children following discrete traumas shows little spontaneous remission [3]. Part of the difficulty is that experiencing trauma at a young age can disrupt typical developmental processes, so higher levels of mood and behavioural problems are seen in comparison to control groups, increased difficulty coping with frustration, bouts of intense fear, sleep disturbances, regression in developmental achievements and social withdrawal [14], which can obviously lead to cumulative difficulties if left untreated.

The National Institute for Health and Care Excellence (NICE; [15]) guidelines recommend psychological treatment for PTSD, the 'gold standard' of which is trauma-focused cognitive behavioural therapy (TF-CBT). Importantly, the guidelines acknowledge that there is currently no evidence base for TF-CBT in younger children [15]. Despite clear clinical demand, the majority of children with PTSD go untreated. There is now an urgent need for the development of an evidence base for treatment of PTSD in young children. The current study meets this need.

Research evaluating TF-CBT in older children and adults has established an empirical base supporting the efficacy of the intervention [16]. Given the rapid development seen in younger children it is necessary to evaluate this paradigm separately to adults and older children. To date, there has only been one small pilot clinical trial examining TF-CBT in younger children, where children were allocated either to receive 12 sessions of manualised TF-CBT or to a waitlist control group [17]. The results of this study, conducted in New Orleans, USA, supported the feasibility and impact of developmentally-tailored CBT with a large effect size and treatment gains maintained at the 6-month follow-up. However, the results from this study are unlikely to be generalisable, particularly within the UK, given that the trial was conducted in an underprivileged, low social-economic group in an urban American setting [17]. Based on our previous work with older children and adolescents, aged 8 to 17 years, showing that TF-CBT improves symptoms of PTSD, anxiety, and depression, as compared to a waitlist control group, we adapted this programme [18] to provide a 12-session intervention suitable for young children (TF-CBT-YC) aged 3 to 8 years, following a single-incident traumatic event.

This study has been designed to answer three main questions. First, do children, diagnosed with PTSD, experience symptom reduction to sub-clinical levels following TF-CBT-YC? Secondly, is the treatment feasible and acceptable? Thirdly, is the cost of implementing TF-CBT-YC likely to represent a saving to the UK National Health Service (NHS) in terms of reducing the overall costs associated with service use post-trauma?

## Methods/Design

### Study design

This study is a two-arm pilot randomised controlled trial (RCT) comparing TF-CBT-YC with treatment as usual (TAU). A half-crossover design will be employed such that participants allocated to the TAU arm will be offered the intervention after a 12-week waiting period if still indicated. Participants will be assessed 4 times during the study - at baseline, at post-TAU or -treatment, and at 3-month and 12-month follow-up for participants allocated to the treatment condition (see Figure 1). The post-treatment assessment will be conducted in the week following treatment completion and the post-TAU assessments will be at a comparable duration in the TAU arm.

**Figure 1 Fig1:**
[figure not shown]
**Participant flow diagram.**

### Participants

A total of 44 children aged 3 to 8 years with a principal diagnosis of PTSD will be randomised to either TAU (n = 22) or TF-CBT-YC (n = 22). For study inclusion, participants will meet criteria for a diagnosis of PTSD for children 6 years and younger according to the DSM-5 [4], as assessed using the Diagnostic Infant and Preschool Assessment (DIPA; [19]). Eligible participants will have experienced a discrete stressor (for example, accident, witnessing or experiencing violence, medical emergency or procedure). Children with both acute (1 to 6 months post-trauma) and chronic (>6 months post-trauma) PTSD will be included, given that there is evidence that TF-CBT-YC benefits both groups [17].

Exclusion criteria comprise head trauma (Glasgow Coma Score < 8); learning disability, but not specific learning difficulties; autism; another primary psychiatric diagnosis that warrants treatment using a psychological therapy ahead of the traumatic stress response; inability to speak English within the family; ongoing exposure to threat; and history of organic brain damage. Victims of chronic sexual or physical abuse will not be invited into the trial because of the need to involve specialist services. Appropriate referrals will be made in this case.

### Determination of sample size

Although a standard power calculation based on detecting treatment effects is the conventional approach to determining sample sizes for definitive clinical trials, the main aim of the current pilot trial is to investigate the core protocol and procedural uncertainties, in preparation for a later scaled up evaluation of the intervention in line with current guidance [20]. Nonetheless, we will obtain working knowledge of the likely effect size of the intervention itself. Seventeen participants per arm (TF-CBT-YC versus TAU) is enough to detect a difference in the recovery percentage as small as 44% on the DIPA diagnosis of PTSD, with 80% power at the 1-tailed 5% level of significance (45% in TAU versus 89% in TF-CBT-YC). These figures fall within the intent-to-treat outcomes in our previous trial in older children [18] (WL: 42% versus TF-CBT: 92%). These group sizes would also detect differences as small as 1.0 standard deviation (SD) unit on our continuous outcome of PTSD symptomatology, given the same power and level of significance. This would have provided sufficient power to detect group differences both in our previous trial [18] (adjusted effect size: Child PTSD Symptom Scale [21] = 2.48 SD units) and in the New Orleans trial [17] (adjusted effect size: PTSD symptom count = 1.32 SD units). To account for 20% potential attrition we will, therefore, recruit 22 young children per arm to the trial. It is important to note that the use of a half-crossover design with the initial TAU participants being offered TF-CBT-YC augments the sample size for the pre- to post-treatment comparisons on outcomes.

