### Statistical analysis plan

Initial analyses of the quantitative primary and secondary outcome data will be conducted on an intent-to-treat basis, with subsequent analyses being per protocol (based on attendance at 50% of offered sessions), and carried out by the trial statistician (PW) following CONSORT standards [33]. Comparisons will be made across groups on all outcome measures. For the continuous scales, repeated measures analyses of variance (ANOVAs) will be used without adjustment in the first instance, and then adjusting for baseline levels of the relevant measures as covariates if indicated. For the caseness measure of PTSD, non-parametric analyses will be used (for example, Chi square/Fisher’s exact test).

Qualitative interview data will be analysed using thematic analysis [34], facilitated by NVivo 8 software (QSR International). For the health economic data, mean estimated treatment costs in the two trial arms will be compared using ANOVA and the robustness of the parametric tests confirmed using bootstrapping. The primary analysis will explore cost-effectiveness in terms of loss of PTSD diagnosis (that is 'recovery'). If a significant difference in the primary outcome is observed between the two treatment arms, cost-effectiveness will be explored through calculation of an incremental cost-effectiveness ratio and sensitivity analyses.

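### The 1.0 SD detectable difference does not fit the 1-tailed 5% level it is stated at: 17 per arm then detects about 0.87 SD, and 1.0 SD is the two-sided figure (minor, no change in n)

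*Protocol article*

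**What the plan says.** The section on determination of sample size (protocol article) takes 17 evaluable children per arm and claims a detectable difference in recovery from PTSD on the DIPA "with 80% power at the 1-tailed 5% level of significance", for "45% in TAU versus 89% in TF-CBT-YC". It then turns to the continuous outcome and says the same group sizes would detect differences "as small as 1.0 standard deviation (SD) unit on our continuous outcome of PTSD symptomatology, given the same power and level of significance". By that wording the second figure is also an 80% power, 1-tailed 5% figure. The section next compares it with effect sizes of 2.48 SD and 1.32 SD from two earlier trials, and closes with the attrition step: "To account for 20% potential attrition we will, therefore, recruit 22 young children per arm to the trial".

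The article's statistical analysis section gives no sidedness. For the diagnosis it says "For the caseness measure of PTSD, non-parametric analyses will be used", with chi-square and Fisher's exact test as examples. For the scales it names repeated measures ANOVA.

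**The concern.** A reader who recalculates the continuous figure under the stated conditions does not get 1.0 SD. The number matches a two-sided test, while the text ties it to the 1-tailed level of the binary calculation. One sentence of the design justification therefore disagrees with the one it refers back to, and the intended significance level becomes uncertain for both outcomes.

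This calculation is the only quantitative basis given for 17, and then 22, per arm. Sidedness also matters later: the article makes the incremental cost-effectiveness ratio conditional on a significant difference in the primary outcome, so the level at which significance is judged should be clear.

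**Working it through.** **Inputs**, all from the section on determination of sample size: n = 17 per arm, equal allocation; power 80%; alpha 5%, 1-tailed; recovery 0.45 versus 0.89; continuous difference 1.0 SD; attrition 20%.

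**1. Attrition.** 17 / (1 − 0.20) = 21.25, rounded up to 22. This reproduces.

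**2. Binary figure as labelled.** Power was found by enumerating all 18 × 18 outcomes of Bin(17, 0.45) and Bin(17, 0.89) and summing the probability of those with p ≤ 0.05:

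| Test, 17 per arm | 1-tailed 5% | Two-sided 5% |
|---|---|---|
| Fisher's exact | 81.4% | 70.3% |
| Chi-square, continuity-corrected | 81.4% | 70.0% |
| Chi-square, uncorrected | 89.7% | 81.4% |

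The stated 80% reproduces at 1-tailed 5% with Fisher's test or the corrected chi-square. It reproduces equally well at two-sided 5% with the uncorrected chi-square.

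The usual formula for the uncorrected test agrees:

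n = [z_α √(2p̄q̄) + z_β √(p₁q₁ + p₂q₂)]² / (p₂ − p₁)²

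Here p̄ = 0.67, √(2 × 0.67 × 0.33) = 0.665, √(0.2475 + 0.0979) = 0.588 and (0.44)² = 0.1936.

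- Two-sided: (1.960 × 0.665 + 0.842 × 0.588)² / 0.1936 ≈ 16.7, so 17 per arm.
- 1-tailed: (1.645 × 0.665 + 0.842 × 0.588)² / 0.1936 ≈ 13.0 (just above 13), so 14 per arm.

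**3. Continuous figure as labelled.** The normal approximation for the smallest detectable standardised difference is d = (z_α + z_β) √(2/n), with √(2/17) = 0.343:

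- 1-tailed: (1.645 + 0.842) × 0.343 = 0.85 SD.
- Two-sided: (1.960 + 0.842) × 0.343 = 0.96 SD.

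With the noncentral t distribution (32 degrees of freedom):

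| 17 per arm | Detectable at 80% power | Power at 1.0 SD |
|---|---|---|
| 1-tailed 5% | 0.87 SD | 88.6% |
| Two-sided 5% | 0.99 SD | 80.7% |

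The stated 1.0 SD does not reproduce at 1-tailed 5%. Rounding does not explain the gap: at that level 1.0 SD needs only 14 per arm (82.4% power). It does reproduce at two-sided 5%.

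**4. Which statement is wrong.** Two readings fit the numbers.

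- The binary calculation is a 1-tailed Fisher or corrected chi-square test and the continuous one is a two-sided t-test. The 1.0 SD is then wrong under its label.
- Both calculations are two-sided 5% (uncorrected chi-square and t-test, each needing 17 per arm). The 1-tailed label is then wrong for both.

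The article does not allow a choice between them.

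**The case against.** The strongest reply is that nothing depends on the slip. It is conservative: at the stated level 17 per arm has more power for 1.0 SD than claimed. The figure serves only to show that effects of 2.48 SD and 1.32 SD would be detected, and both exceed 0.87 and 0.99 SD. The section itself says that the pilot's main purpose is to settle procedural uncertainties, not to power an efficacy test. All of this stands, and it is why the point is minor. It does not make the printed figure correct.

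A reader might go further and infer that the primary analysis really has 70% power instead of 80%. The documents do not support that. The 80% is stated as 1-tailed and reproduces on those terms. The 70.3% needs a two-sided Fisher test, which the article does not specify; its analysis section names Fisher's and chi-square tests only as examples. Moreover, 17 is the number left after 20% attrition: with all 22 per arm analysed, even a two-sided Fisher test has 84.5% power. The 70% is a sensitivity result.

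Nor is the open choice of test and sidedness in the analysis section an error in itself. This is a condensed article, and a fuller analysis plan may settle it.

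**Conclusion.** The concern holds as an inconsistency within the sample-size section. At 80% power and 1-tailed 5%, 17 per arm detects about 0.87 SD, not 1.0 SD; the printed figure is the two-sided one. Either that figure or the 1-tailed label needs correcting. That the section mixes two conventions is one possible reading and is not established, because both figures also fit two-sided 5% throughout.

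The discrepancy is about 0.13 SD in the detectable difference, or 88.6% against the claimed 80% power at 1.0 SD. It errs on the safe side, and 17 and 22 per arm both stand. Severity is minor.

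The check assumes an unadjusted comparison of two means with equal variances and 17 per arm. A repeated measures analysis would also depend on the correlation between baseline and follow-up, which the article does not give and does not invoke for this figure.

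**What to change.** Use one sidedness for both calculations in the sample-size section and carry it into the primary test in the statistical analysis section. There are two consistent options:

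- **Keep 1-tailed 5%.** Restate the continuous detectable difference as about 0.87 SD, and say that the primary test is a 1-tailed Fisher or continuity-corrected chi-square test (81.4% at 17 per arm).
- **Label both calculations two-sided 5%.** The 1.0 SD then stands, and 45% versus 89% has about 81% power with the uncorrected chi-square, which should be named as the primary test. Note that a two-sided Fisher test would give about 70% at 17 per arm, or about 85% if all 22 per arm are analysed. Note also that the uncorrected chi-square is not exact: at 17 per arm its true two-sided error rate can reach 5.8%.

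The authors know which calculation was run and should choose accordingly. The cost is about two sentences of wording, with no change in sample size.

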### Recruitment

There are two pathways through which participants will be recruited. The first is via an embedded prospective longitudinal study of trauma-exposed children, who have attended EDs in East Anglia, UK. Children attending EDs in hospitals in East Anglia after a single- event trauma (typically a road traffic accident or assault, but also including falls and other accidental or medical injuries) will be invited to take part in a screening study component of this project. Initially, parents of children exposed to a discrete trauma satisfying the study inclusion criteria will be sent details of the study by post and then contacted by a member of the ED team within 1 to 2 weeks post-trauma to assess eligibility and to obtain verbal consent to take part in this prospective longitudinal study. Consenting families will then be contacted at 2 to 4 weeks and again at 3 months post-trauma, at which point participants meeting a diagnosis of PTSD will be invited into the trial.

The second pathway through which participants will be recruited is via referral from community sources, including Child and Adolescent Mental Health Services (CAMHS), schools, Victim Support agencies, General Practitioners, the police (for example, Family Liaison Officers) and advertisements placed in local newspapers, on the Internet, in children’s centres and doctors surgeries.

### Participant allocation

Eligible participants will be randomised to TF-CBT-YC or TAU using a minimisation procedure suitable for small samples, constrained by age group (3 to 5 years or 6 to 8 years), gender, and initial clinical severity as assessed on the DIPA (high and low). These variables were selected because of their likely influence on treatment response. Randomisation will occur after consent has been taken and baseline measures have been completed. The trial team will Email the independent statistician (PW) details of the three stratifiers and, using the minimisation programme MinimPy [22], the statistician will randomise the participant and Email the results to the trial coordinator. Following randomisation, participants will be notified of their allocation by telephone, which is subsequently confirmed in writing. See Figure 2 for the Consolidated Standards of Reporting Trials (CONSORT) diagram.

**Figure 2 Fig2:**
[figure not shown]
**Trial Consolidated Standards of Reporting Trials (CONSORT) diagram.**

### Interventions

TF-CBT-YC is a structured, manualised treatment, adapted from a treatment package developed for a previous trial of CBT for chronic PTSD (that is symptoms for > 6 months) in children and adolescents [18]. This treatment is based on a cognitive conceptualisation of PTSD [23,24] and specifically targets three maintaining factors of the disorder that are implicated in the aetiology of PTSD in youth: trauma memories, negative appraisals and maladaptive coping [23].

TF-CBT-YC is delivered to the child and parent or caregiver over 12 sessions of 60 to 90 minutes, supplemented by homework tasks. TF-CBT techniques for this age group have been derived both from our own published protocol for older children and adolescents developed for a previous trial [25], as well as the New Orleans protocol, used in the only published RCT for PTSD in this age group [17]. Treatment materials for this trial are developmentally sensitive with more complex cognitive exercises being introduced for the older children, as appropriate, in the 6 to 8 year age range. Specific techniques for the child and/or parent/caregiver include education about PTSD, recognition of feelings, training in coping skills, graduated exposure to the trauma through imagery, drawings and *in-vivo* work, the development of a coherent trauma narrative, the identification and reappraisal of erroneous trauma-related beliefs, and safety planning. Three sessions take place with the child and parent/caregiver together. The remaining sessions are divided into two halves. The first half involves the therapist and child only, but information is shared with the parent or caregiver via the therapist with the child’s knowledge. This facilitates parallel learning of the material and caregiver’s attunement to the child’s needs and feelings. The second half of each session involves just the therapist and parent or caregiver and provides a forum to discuss any problems, to assist the therapist in developing an understanding of the child’s behaviour outside of the session, and to plan and troubleshoot the homework assignments.

Participants in the TAU arm do not initially receive any TF-CBT from the trial team. However, they are able to continue any therapeutic input they have already during this period, and any for which they are newly referred, and if at post-treatment assessment the child still meets criteria for PTSD, they are then offered TF-CBT-YC, exactly as described above.

